### Sample size calculation

2.6

Separate sample size calculations were performed for the two primary endpoints tolerability and efficacy. The type I error of 0.05 was distributed between both outcomes.

For non-inferiority of tolerability, the non-inferiority margin for dose reductions due to toxicity was set at 24 %. With a type I error of 0.01, power of 80 %, and an incidence of dose reductions of 28 % in each group [31], 71 patients need to be randomised to each treatment group. The non-inferiority margin for tolerability of 24 % is relatively large. This has been extensively discussed with the clinicians and patient advocates experienced in the treatment with olaparib. The most prominent adverse events related to olaparib therapy are anaemia and gastro-intestinal symptoms [35]. Since patients who start olaparib are initially closely monitored, these adverse events are usually detected shortly after start of olaparib and are easily and effectively managed with dose reductions. Therefore, the clinical impact of these side effects is acceptable, and the larger non-inferiority margin of 24 % was accepted.

For non-inferiority of efficacy, the non-inferiority margin for PFS rate at twelve months was set at 15 %. With a type I error of 0.04, power of 80 %, and an estimated PFS at twelve months of 88 % in each group, 64 patients need to be randomised to each treatment group [31]. The non-inferiority margin for efficacy of 15 % was set according to the EMA guideline [36]. The margin demonstrates superiority to placebo as olaparib increased progression-free survival at 12 months by 33 % compared to placebo [31]. Moreover, the non-inferiority margin has been discussed and endorsed by clinicians and patient advocates.

Thus, the total sample size was set at 142 patients, of which 128 will receive olaparib for high-grade, BRCA-mutated ovarian cancer after response on first-line platinum-based chemotherapy.

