## Abstract

**Background:**

Pharmacokinetic (PK) boosting is the intentional use of a drug-drug interaction to enhance systemic drug exposure. PK boosting of the anticancer drug olaparib, a CYP3A-substrate, has the potential to reduce PK variability, side effects and financial burden associated with this drug. After establishing adequate pharmacokinetic exposure with boosting in the PROACTIVE-A study, the PROACTIVE-B study is designed to evaluate non-inferiority for both efficacy and toxicity of the boosted therapy compared to the standard monotherapy of olaparib.

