### Objectives

2.2

The primary objective of this study is to determine if boosted olaparib therapy is non-inferior to standard monotherapy concerning both tolerability and efficacy. Tolerability will be measured by dose reductions due to toxicity. Efficacy will be measured by progression-free survival (PFS) in patients with high-grade serous BRCA-mutated ovarian cancer treated with olaparib maintenance therapy after first-line platinum-based chemotherapy.

Secondary objectives include establishing potential differences in type of toxicity, patient health status, therapy satisfaction, cost-effectiveness between treatment arms. Moreover, the predictive value of circulating tumour DNA (ctDNA) as a pharmacodynamic response marker will be evaluated. Exploratory objectives include the association between olaparib PK and toxicity and efficacy, and the association between patient characteristics and olaparib PK and efficacy. Finally, differences in intratumoral olaparib concentrations between treatment arms will be explored.

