### Endpoints and assessments

2.3

The co-primary endpoints are dose reductions due to toxicity and PFS, defined as the time from randomisation until the date of either objective radiological disease progression or combined biochemical and clinical progression or death. The reasons for dose reductions will be recorded. Objective radiological disease progression will be assessed according to the Response Evaluation Criteria in Solid Tumours (RECIST) version 1.1, or modified RECIST according to the Gynecologic Cancer Intergroup (GCIG) if there is no measurable disease at baseline [22,23]. Biochemical progression is assessed according to the GCIG criteria for CA-125 and clinical progression will be established by the treating physician [23].

For toxicity, adverse events will be scored according to the Common Terminology Criteria for Adverse Events (CTCAE) version 5.0 [24]. Patient health status and quality of life will be measured with the EuroQol 5 dimensions 5 levels questionnaire (EQ-5D-5L) version 1.1 [25]. Patient satisfaction in terms of cancer therapy will be assessed with the Cancer Therapy Satisfaction Questionnaire (CTSQ) [26]. To measure costs from the societal perspective for the cost-effectiveness analysis, the Institute for Medical Technology Assessment (iMTA) Productivity Cost Questionnaire (iPCQ) and iMTA Medical Consumption Questionnaire (iMCQ) will be used [27,28]. ctDNA levels in plasma will be measured with shallow Whole Genome Sequencing (sWGS) and/or a hybrid-capture based Next Generation Sequencing (NGS) panel, dependent on the most recent insights at time of analysis. ctDNA levels will be corrected for germline and clonal haematopoietic variants with matched peripheral blood mononuclear cells. Olaparib plasma concentrations will be measured by cross-validated liquid chromatography tandem mass-spectrometry assays [21,29,30]. Intratumoral olaparib concentrations will be assessed from optional tumour biopsies. The frequency of the above-mentioned assessments is outlined in Table 2.

**Table 2 tbl2:** Overview of measurements in PROACTIVE-B study.

	Baseline	Week 4	Week 6	Week 8	Week 12	Every 3 months	Every 6 months	At progression
Clinical evaluation	X	X		X	X	X	X	
Laboratory	X	X		X	X	X	X	
Adverse events	X	X		X	X			
Radiological evaluation	X				X		X	
ctDNA	X	X		X	X			X
Plasma olaparib PK		X		X	X			
Intratumoral olaparib PK				X				X

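### The type I error is split 0.01/0.04 although the objective is non-inferiority on both endpoints; the split only costs power, and the power for the joint objective, about 65%, is not reported

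*Protocol article*

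**What the plan says.** The Objectives section gives the primary objective as to "determine if boosted olaparib therapy is non-inferior to standard monotherapy concerning both tolerability and efficacy". The abstract says likewise that the study is "designed to evaluate non-inferiority for both efficacy and toxicity of the boosted therapy". Under Endpoints and assessments, "The co-primary endpoints are dose reductions due to toxicity and PFS".

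The Sample size calculation section sizes each endpoint separately and states that "The type I error of 0.05 was distributed between both outcomes".

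- **Tolerability:** "the non-inferiority margin for dose reductions due to toxicity was set at 24" per cent. "With a type I error of 0.01, power of 80 %, and an incidence of dose reductions of 28 % in each group", the result is 71 patients per arm.
- **Efficacy:** type I error 0.04, power 80%, 12-month PFS of 88% in each arm and a 15-point margin give 64 patients per arm.

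The article gives no power for meeting both endpoints. It has no explicit rule saying whether success needs both tests or one, and it does not say whether the levels are one-sided or two-sided.

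**The concern.** The objective and the error allocation answer different questions. Dividing 0.05 into 0.01 + 0.04 protects a trial that may claim success if either endpoint is met. A trial that claims success only when both are met has the opposite problem: its overall error is already controlled, and its power falls because two tests must be won.

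Two things are at stake. The reader is given no figure for the chance that the trial meets its stated objective. And part of the shortfall is avoidable without recruiting anyone, because the strictest level (0.01) falls on an endpoint where the requirement to win both gives no reason for it.

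**Working it through.** **Inputs** (Sample size calculation section): tolerability p = 0.28 in each arm, margin d = 0.24, level 0.01, 71 per arm; efficacy p = 0.88 in each arm, d = 0.15, level 0.04, 64 per arm. Allocation is 1:1 (Design section).

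**Step 1. Reproduce the stated sizes.** n per arm = 2p(1-p)(z_α + z_β)² / d², unpooled variance, true difference zero.

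- Tolerability, one-sided 0.01: 2(0.28)(0.72)(2.326 + 0.842)² / 0.24² = 70.3, so 71.
- Efficacy, one-sided 0.04: 2(0.88)(0.12)(1.751 + 0.842)² / 0.15² = 63.1, so 64.

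Both match. Read as two-sided, the levels would need 82 and 79. The plan's levels are therefore one-sided.

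**Step 2. Error control when both must succeed.** The joint claim is false if at least one endpoint is truly worse by its margin or more. Claiming success wrongly then requires rejecting that endpoint's null hypothesis, which happens with probability no greater than that test's own level. With each test at 0.05, the overall error is at most 0.05 (the intersection-union principle). With the split it is at most max(0.01, 0.04) = 0.04, so the plan does not use its full allowance.

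**Step 3. Power at the planned sizes.** Power = Φ(d / √(2p(1-p)/n) - z_α).

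- Tolerability: standard error √(0.4032/71) = 0.0754, and 0.24/0.0754 = 3.185.
- Efficacy: standard error √(0.2112/64) = 0.0574, and 0.15/0.0574 = 2.611.

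| One-sided levels (tolerability / efficacy) | Tolerability | Efficacy | Both, if independent | Both, correlation -0.3 to 0.5 |
|---|---|---|---|---|
| 0.01 / 0.04 (plan) | 80.5% | 80.5% | 64.8% | 62.8% to 69.4% |
| 0.05 / 0.05 | 93.8% | 83.3% | 78.2% | 77.5% to 80.3% |
| 0.025 / 0.025 | 89.0% | 74.3% | 66.1% | 64.5% to 69.7% |

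The article gives no correlation between the endpoints, so the range in the last column is an assumption. Whatever the correlation, joint power under the plan lies between 0.805 + 0.805 - 1 = 61% and 80.5%.

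**Step 4. Where the miss probability comes from.** Planned: 100 - 64.8 = 35.2 points. Without the split: 100 - 78.2 = 21.8 points. The split therefore accounts for 35.2 - 21.8 = 13.4 points. Moving tolerability alone to 0.05 gives 0.938 × 0.805 = 75.5%, a gain of 10.7 points. So about 11 of the 13 points come from the 0.01 level.

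**The case against.** Several points on the other side have force.

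- **The 80% is not misreported.** A reader might infer that the article claims 80% power for the joint objective. It does not: it says the calculations were separate, and each figure is right on its own terms. The joint power is unreported, not wrong.
- **The success rule is inferred.** The objective says what will be evaluated, not what counts as winning, and the split may itself signal that separate claims are intended. The full protocol may settle this. What stands is that the word both, in the abstract and the objective, does not fit an either-suffices allocation. One of the two needs changing or explaining.
- **The split is conservative.** It does not inflate the type I error or bias an estimate. A strict level on tolerability can also be defended, since the Discussion calls it uncertain whether higher exposure will increase adverse events. That could be a reason to choose 0.01 deliberately, but the article gives the division of 0.05 between outcomes as the basis.
- **The 0.01 level is not the main cause.** A reader might infer that most of the one-in-three chance of missing comes from it. It explains about 11 of 35 points.
- **The 24-point margin is a separate matter.** A reader might infer that the 0.01 level produced the wide margin. The article justifies that margin on clinical grounds and by stakeholder discussion, and nothing in it ties the margin to the level.

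Leaving the sidedness label to a fuller document is no fault in itself, since the sample sizes identify the levels.

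**Conclusion.** The mismatch is real and moderate. Read as the objective is worded, the split is unnecessary and costs about 13 points of joint power, 65% against 78% with the same patients. The larger part of the miss probability, about 22 of 35 points, would remain without the split, because two tests must be won.

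These figures assume identical true rates in the two arms, the planned rates of 28% and 88%, the plan's own formula with one-sided levels, and independence (63% to 69% as planned over the assumed correlations). If 0.01 and 0.04 were meant as two-sided, power would be about 73% and 71%, and joint power about 52%. That both tests must succeed is a reading of the objective, not a rule the article states.

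The point should be fixed. It is not a fatal flaw: a trial that meets both criteria under the split would support its conclusion at least as firmly as one tested without it.

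**What to change.** State in the Sample size calculation section that success requires both non-inferiority tests. Drop the split, test each endpoint at the plan's full level of 0.05, labelled one-sided, and report the joint power of about 78% with its assumptions. No extra patients are needed.

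If the split is kept, either report about 65% as the power for the joint objective or state that separate claims are intended and reword the objective to match. For comparison, keeping the split and reaching 80% joint power under independence would take about 90 patients per arm for tolerability and 85 for efficacy, that is 180 in total with 170 in the ovarian group.

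Costs and limits:

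- The tolerability test becomes looser than 0.01.
- The trial is ongoing and open-label, so the change must be made by amendment before any comparison of outcomes between arms.
- One-sided 0.025 on each endpoint is possible, but it gives only about 66% joint power and lowers efficacy power to 74%, below the plan's own 80% target.
- Using the freed error to narrow the tolerability margin to about 19 points at 80% power would spend the gain: 0.80 × 0.833 is about 67% joint power, close to the present figure.

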### Statistical analysis

2.7

An intention-to-treat, and per protocol, analysis will be performed in line with guidelines. The per-protocol analysis will be leading, but it is not expected that cross-over will take place. Proportions of patients with dose reductions due to toxicity at twelve months will be compared between both treatment arms with the Chi-square test for proportions. Additionally, a Kaplan-Meier approach will be used to compare PFS rates between both treatment arms in the efficacy population.

Linear mixed-effects models will be used to evaluate differences in patient health status and therapy satisfaction over time and between treatment arms. Descriptive statistics will be used to describe adverse events and intratumoral olaparib concentration. The association between ctDNA levels and clinical outcomes (PFS/OS) will be explored with a Cox proportional hazard model with a correction for previously defined prognostic factors [37]. Additionally, cost-effectiveness will be analysed in line with the most recent guideline for economical evaluations in healthcare by the Dutch Healthcare Institute [38]. In line with this guideline, we will adopt a societal perspective and a life time horizon to calculate the costs per quality adjusted life year (QALY) in a cost-utility analysis [38].

The patterns and extend of missing data over time and between treatment arms will be explored. As the primary endpoints are easy to assess, missing data is expected to be minimal for the primary analysis. In case of unexpected high proportions of missing data or missing data that can be classified as Missing Not At Random (MNAR), imputation methods and/or sensitivity analyses will be applied [39].

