### Design

2.1

PROACTIVE-B is a Dutch nationwide, open-label, randomised, multicentre trial comparing boosted olaparib therapy with standard dose olaparib monotherapy in patients with solid tumours (Fig. 1). Patients will be randomised 1:1 between standard olaparib monotherapy and the boosted therapy of olaparib and cobicistat by a variable block randomisation. Randomisation will be stratified by tumour type (BRCA-mutated, high-grade, serous ovarian cancer treated with olaparib after first-line platinum-based chemotherapy, or other) and response to chemotherapy (i.e., complete, or partial response). The standard full dose of olaparib monotherapy consists of 300 mg BID. The boosted full dose of olaparib consists of 100 mg BID with cobicistat 150 mg BID. Dose reductions will be performed according to Table 1, in line with the drug label and the physician's discretion. Patients will visit the outpatient clinic at baseline, after 4, 8, 12 weeks and thereafter every three months until progression or the end of olaparib therapy, in line with standard clinical care. Patients will continue treatment until they do not longer experience clinical benefit or until the end of treatment according to the drug label and/or treatment guideline. This current protocol is approved by the Medical Research Ethics Committee Oost-Nederland and is conducted in accordance with Good Clinical Practice and the Declaration of Helsinki.

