To ensure feasibility of the protocol, this study is aligned with the current standard clinical practice as much as possible. Additional follow-up visits outside the study protocol are accepted and monitored for adverse event reporting as well. Questionnaires will be sent out online to reduce burden for the clinic and research staff, but also to make it as convenient as possible for patients who can fill in the questionnaires at a moment that fits them best.

The wide inclusion criteria of the study will result in a study population that reflects the real-world population. This will lead to broad external validity of our results. Of note, there is no exclusion criterion for patients treated with comedication that are substrates for CYP3A. These drugs could also be affected by cobicistat and, therefore, patients are screened for drug-drug interactions through routine workflows. Relevant interactions may limit the use of cobicistat. Due to the extensive experience with these drugs in antiretroviral therapy, this is considered a manageable hurdle [40].

Besides the clinical evaluation of the boosted therapy, this study incorporates several emerging research topics. In the past years, ctDNA analysis have provided valuable insights in its clinical validity in several cancer types [41]. In patients with ovarian cancer, ctDNA is correlated with the volume of disease and holds promise as a biomarker for disease monitoring [42,43]. This is interesting, considering the poor concordance between CA-125 and radiological progression in patients treated with PARP-inhibitors [44]. Moreover, reversion mutations could be detected in ctDNA of patients after treatment with olaparib and cediranib, which could provide valuable insights for treatment optimization [45].

Also, tumour biopsies will shed light on the intratumoral olaparib concentration, which might be increased with the boosted therapy and could therefore be a potential tool to convert resistance. Preclinical studies have shown that tumours are able to express CYP3A as a detoxification mechanism [18,20]. By inhibiting CYP3A, PK boosting might even increase intratumoral olaparib concentrations by CYP3A-inhibition and could therefore improve efficacy. The tumour biopsies are optional in this study, but even a small number of biopsies will provide new insights.

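### The per-protocol analysis alone decides both co-primary non-inferiority comparisons, although its exclusions may differ by arm and be related to toxicity; both planned analysis sets should have to agree.

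*Protocol article*

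**What the plan says.** Section 2.7 of the protocol article names two analysis sets: "An intention-to-treat, and per protocol, analysis will be performed in line with guidelines". It then ranks them: "The per-protocol analysis will be leading, but it is not expected that cross-over will take place". No role in the conclusion is given to the intention-to-treat result, and there is no rule for the case where the two sets disagree.

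The tolerability comparison is described as follows: "Proportions of patients with dose reductions due to toxicity at twelve months will be compared between both treatment arms with the Chi-square test for proportions". PFS rates are compared by a Kaplan-Meier approach in the ovarian cancer population.

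Four other places bear on who might leave the per-protocol set:

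- Design (2.1) and Table 1: only the boosted arm receives cobicistat, the trial is open-label, and dose reductions are planned steps ("Dose reductions will be performed according to Table 1, in line with the drug label and the physician's discretion").
- Study population (2.4): known contra-indications to cobicistat exclude a patient from either arm at entry. Event-free patients who withdraw within three months are replaced, up to about 30%.
- Discussion (3), on co-medication: drugs that are CYP3A substrates are not an exclusion, patients are screened for interactions in routine care, and "Relevant interactions may limit the use of cobicistat".
- Discussion (3), on exposure: it is uncertain whether the boosted regimen will cause more adverse events.

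**The concern.** A per-protocol analysis compares patients selected after randomisation. It is a reasonable companion to intention-to-treat in a non-inferiority trial, because non-adherence can make two arms look alike. It is a weak sole arbiter when the reasons for leaving the set differ between arms or are tied to the outcome.

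Both conditions are possible here. Non-use or stopping of cobicistat can occur only in the boosted arm. If patients who leave the regimen because of toxicity are dropped, the tolerability comparison loses people who were likely to have had a dose reduction. The expectation of no cross-over does not address either route.

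At stake is a false declaration of non-inferiority. On tolerability the margin is already wide: "the non-inferiority margin for dose reductions due to toxicity was set at 24" percentage points.

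**Working it through.** **Inputs from the Sample size calculation section (2.6).** Tolerability: "With a type I error of 0.01, power of 80 %, and an incidence of dose reductions of 28 % in each group", margin 24 points, 71 per arm. Efficacy: "With a type I error of 0.04, power of 80 %, and an estimated PFS at twelve months of 88 % in each group", margin 15 points, 64 per arm. The documents give no exclusion or non-use rates, so all such rates below are assumptions.

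**1. Reproduce the stated sizes.** With equal true rates p, margin m and one-sided α:

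n per arm = (z₁₋α + z₀.₈₀)² × 2p(1−p) / m²

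- Tolerability: (2.326 + 0.842)² × 2 × 0.28 × 0.72 / 0.24² = 70.3, rounded up to 71.
- Efficacy: (1.751 + 0.842)² × 2 × 0.88 × 0.12 / 0.15² = 63.1, rounded up to 64.

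Both match. Reading the alphas as two-sided gives 82 and 79, which do not match. The sample size arithmetic is sound with one-sided alphas of 0.01 and 0.04.

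**2. Probability of declaring non-inferiority.** With d the true disadvantage of the boosted arm in the analysed set:

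P = Φ[(m − d)/SE − z₁₋α], where SE² = p_c(1−p_c)/n_c + p_b(1−p_b)/n_b

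**3. Per-protocol error for tolerability.** Put the true rates at the margin: 28% standard, 52% boosted. Exclude a fraction x of the boosted arm, of whom a fraction q would have had a dose reduction. The remaining boosted rate is (0.52 − xq)/(1 − x), with n_b = 71(1 − x).

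Example, x = 0.10:
- q = 0.75: (0.52 − 0.075)/0.90 = 0.494, d = 0.214, SE = 0.082, P = Φ(−2.015) = 2.2%.
- q = 1: (0.52 − 0.10)/0.90 = 0.467, d = 0.187, SE = 0.082, P = Φ(−1.676) = 4.7%.

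| Boosted arm excluded | q = 75% | q = 100% |
|---|---|---|
| 0% | 1.0% | 1.0% |
| 5% | 1.5% | 2.2% |
| 10% | 2.2% | 4.7% |
| 15% | 3.3% | 9.6% |

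If those excluded have the same 52% rate as the arm they leave, the error stays at 1.0%. The inflation comes from selection on toxicity, not from the loss itself. At q = 60% and x = 10% it is only 1.3%.

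**4. Per-protocol error for efficacy.** True 12-month PFS at the margin, 88% v 73%; 10% of the boosted arm excluded, half of them progression-free. The remaining rate is (0.73 − 0.05)/0.90 = 0.756, and the error rises from 4% to 8.3%.

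**5. Intention-to-treat error for tolerability.** Suppose 10% of the boosted arm takes standard olaparib without cobicistat and has the standard-arm rate. The boosted rate is 0.90 × 0.52 + 0.10 × 0.28 = 0.496, d = 0.216, SE = 0.080, P = Φ(−2.025) = 2.1%. At 20% non-use it is 4.2%.

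**6. Power.** At the full randomised numbers it is 80.5% for both endpoints. If 10% is lost from the boosted arm only, unrelated to outcome, it is 78.0% for tolerability and 78.5% for efficacy.

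**The case against.** The strongest case for the plan has four parts.

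- **Dose reductions are part of the protocol.** A reader might infer that a leading per-protocol analysis of tolerability conditions on its own outcome. The text does not support that. A patient whose dose is reduced under Table 1 is compliant and need not leave the set. The article does not define the set, and that detail may properly sit in the full protocol or SAP. What stands is a conditional risk: bias follows if patients are dropped for toxicity-related stopping or changes. The article also does not say that stopping counts as a dose reduction, so restoring stopped patients helps only so far as their events are counted.
- **Interaction-driven non-use can bias the other way.** Step 5 shows that such patients, kept in the boosted arm on standard olaparib, pull the arms together and make intention-to-treat too lenient. This stands. It is a reason to require both sets rather than to swap one sole arbiter for the other.
- **The loss may be small.** Known contra-indications are screened out at entry, and the Discussion regards interactions as manageable. This stands as a limit on size. A reader might also infer that interaction screening happens after randomisation and should be moved forward. Its timing is not stated, so that cannot be claimed.
- **Power is hardly touched.** A reader might apply losses to both arms, but the argument here concerns one arm, where a 10% loss costs about two points. Replacement of early event-free withdrawals also covers part of any loss, though not every per-protocol exclusion. Power is a minor matter.

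**Conclusion.** The point holds in a limited form. Section 2.7 fixes per-protocol as the sole leading analysis for both co-primary endpoints, and the only reassurance concerns cross-over. The article itself describes a regimen component used in one arm, interactions that may limit it, and unresolved toxicity. That is enough to make differential, toxicity-related exclusions plausible; it does not show that they will occur.

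For tolerability, 10% exclusion from the boosted arm takes the type I error from 1.0% to between 2.2% and 4.7%, if 75% to 100% of those excluded would have had a dose reduction. With 10% non-use of cobicistat on standard olaparib, intention-to-treat errs at about 2.1%. Neither set is safe alone. These figures rest on assumed rates, true rates exactly at the margin, and a normal approximation. The stated 71 and 64 per arm are not in error.

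**What to change.** 1. State in section 2.7 that non-inferiority for each endpoint is concluded only if the confidence interval, at that endpoint's one-sided alpha (0.01 or 0.04), excludes the margin in both the intention-to-treat and the per-protocol set.
2. State that patients are not excluded from the per-protocol set because they stopped or changed treatment for toxicity.
3. State in section 2.6 that the 80% power applies to the full randomised numbers, and that a 10% loss from the boosted arm alone would leave about 78%.

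Both analyses are already planned, so this is a change of wording. The cost is a slightly lower chance of success, because two results must agree instead of one.

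### The Chi-square test named for the co-primary tolerability endpoint does not use the 24-point non-inferiority margin on which the trial was sized

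*Protocol article*

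**What the plan says.** Section 2.2 (Objectives) of the Protocol article sets the primary objective as to "determine if boosted olaparib therapy is non-inferior to standard monotherapy concerning both tolerability and efficacy", and adds: "Tolerability will be measured by dose reductions due to toxicity".

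Section 2.6 (Sample size calculation) turns this into a margin hypothesis. It says that "the non-inferiority margin for dose reductions due to toxicity was set at 24" %. It continues "With a type I error of 0.01, power of 80" %, assumes "an incidence of dose reductions of 28 % in each group", and arrives at 71 patients per arm. It does not say whether the 0.01 is one-sided or two-sided.

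Section 2.7 (Statistical analysis) gives one analysis for this endpoint: the twelve-month proportions with a dose reduction due to toxicity "will be compared between both treatment arms with the Chi-square test for proportions". For this comparison the section mentions no margin, confidence limit, shifted null hypothesis or decision rule. No other part of the article supplies one.

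**The concern.** The hypothesis and the test do not match. Section 2.6 needs a test of whether the boosted arm has an excess of 24 points or more. The Chi-square test for proportions, as the term is normally used, asks whether the two proportions are equal. A non-significant result does not show that the excess is below 24 points, and a significant one does not show that it is above.

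The question is a live one here. The Background reports 1.45-fold higher olaparib exposure with boosting in the preceding study. The Discussion says that toxicity is related to exposure and that it is uncertain whether adverse events will increase. If real excess toxicity is possible, a non-significant difference must not be taken to mean no worse.

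**Working it through.** **Inputs.** Section 2.6: 28% in each arm, margin 24% (taken as percentage points), type I error 0.01, power 80%, 71 per arm. Section 2.1: 1:1 allocation. Section 2.7: twelve-month proportions, Chi-square test.

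**Step 1: reproduce the plan's figure.** For a non-inferiority test on a risk difference with true difference zero,

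n per arm = 2p(1 − p)(z₁₋α + z₁₋β)² / M²

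- One-sided 0.01: 2 × 0.28 × 0.72 × (2.326 + 0.842)² / 0.24² = 0.4032 × 10.036 / 0.0576 = 70.25, so 71. This matches the article.
- One-sided 0.005 (two-sided 0.01): 81.75, so 82. This does not match.
- A test of equality sized to detect 28% v 52% at 0.01 would need 83 (one-sided) or 96 (two-sided). Neither matches.

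The 71 per arm therefore comes from a one-sided 0.01 test against a 24-point margin.

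**Step 2: behaviour of the margin test at 71 per arm.** Conclude non-inferiority if d + 2.326 × SE(d) < 0.24, where d is boosted minus standard. By exact binomial enumeration with the unpooled standard error:

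- power at 28% v 28% is 80.8% (normal approximation 80.5%);
- a false conclusion at 52% v 28% has probability 0.9%.

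**Step 3: behaviour of the Chi-square test at 71 per arm.** The article does not say how its result leads to a conclusion, so both possible readings are shown.

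- *Non-significance at two-sided 0.01 taken as non-inferiority.* At a true 52% v 28%, the standard error under equality is √(2 × 0.40 × 0.60 / 71) = 0.0822 and the true standard error is √((0.52 × 0.48 + 0.28 × 0.72) / 71) = 0.0797. The chance of non-significance is about Φ((2.576 × 0.0822 − 0.24) / 0.0797) = Φ(−0.35) ≈ 0.36. Exact enumeration gives 36.0%.
- *Significance in favour of boosting required.* At equal 28% rates this is one tail of a two-sided 0.01 test, about 0.5%. Exact enumeration also gives 0.5%.

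| Rule at 71 per arm | Passes at 52% v 28% | Passes at 28% v 28% |
|---|---|---|
| Planned | 1% | 80% |
| Margin test, one-sided 0.01 | 0.9% | 80.8% |
| Chi-square not significant at 0.01 | 36.0% | 99.0% |
| Chi-square significant for boosting at 0.01 | – | 0.5% |

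**Step 4: two possible results**, 20/71 on standard in each case.

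- Boosted 24/71: d = 4/71 = 0.056, SE 0.0775, Chi-square p = 0.47. Upper limit 0.056 + 2.326 × 0.0775 = 0.237, below 0.24, so non-inferiority is shown.
- Boosted 32/71: d = 12/71 = 0.169, SE 0.0796, Chi-square p = 0.037. Upper limit 0.169 + 2.326 × 0.0796 = 0.354, above 0.24, so non-inferiority is not shown.

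Neither p-value is significant at 0.01, yet the correct conclusions are opposite.

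**The case against.** The case on the other side has four parts.

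- **The article is condensed.** A margin-shifted score statistic is also of chi-square type, and the full protocol or SAP may define one. This tempers certainty, but nothing shown points that way. The fault is also not a detail left out: the article names a specific test, and its ordinary meaning does not fit the hypothesis.
- **The 36% rests on a decision rule that the article never states.** This stands. It is the consequence of one natural misreading and not a planned error rate.
- **A reader might infer that the Chi-square test can never show non-inferiority.** That goes too far. A significant result with fewer dose reductions on boosting would put the upper limit well under +24 points. The difficulty is that this route succeeds only about 0.5% of the time under the design's own assumption of equal rates.
- **A reader might extend the criticism to efficacy or to missing data.** The documents do not support either. For progression-free survival, section 2.7 says that "a Kaplan-Meier approach will be used to compare PFS rates between both treatment arms in the efficacy population". That approach can yield a twelve-month difference with a confidence interval, and leaving the 15-point margin unrepeated there is ordinary condensation. Unknown twelve-month status affects any comparison of simple proportions, including a margin-based one, and section 2.7 provides for imputation and sensitivity analyses.

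**Conclusion.** Wrong as written, and confined to the test named for tolerability. Section 2.7 names a test that, in its ordinary sense, does not address the hypothesis of section 2.6. It therefore does not provide the planned 1% error or 80% power: depending on how its result is read, the error at the margin is about 36% or the power at equal rates is about 0.5%.

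These figures assume 71 evaluable patients per arm, 28% on standard treatment, the 24% margin as absolute points and a Pearson Chi-square at two-sided 0.01 without continuity correction. The margin itself, the sample size and the efficacy analysis are not called into question by this point.

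**What to change.** In section 2.7, and in the SAP to match, replace the Chi-square test for tolerability with a margin-based rule. Non-inferiority is concluded if the upper limit of the two-sided 98% confidence interval for the twelve-month risk difference in toxicity-related dose reduction, boosted minus standard, is below +24 percentage points. Name a score method, such as Farrington-Manning or Miettinen-Nurminen.

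State in section 2.6 that the 0.01 is one-sided. That is inferred here because it is the reading that reproduces 71 per arm; at two-sided 0.01 the same formula asks for 82.

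The cost is a change of wording, to be made before the data are analysed. It needs no more patients and no further data: the unpooled formula gives 71 per arm, and the Farrington-Manning version gives 69.5, so 70.
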